**Methods/design:**

In this study, a randomized, double-blind, double-dummy, parallel control of positive drug, multicenter clinical study will be established. A total of 252 patients with acute uncomplicated lower UTI (syndrome of dampness-heat in the lower jiao) will be randomly allocated in the ratio of 1:1:1 to three groups: experimental group; control group 1; and control group 2. The experimental group receives Sanjin tablets plus levofloxacin tablets (LT) placebo; the control group 1 receives LT plus SJT placebo; and the control group 2 receives SJT plus LT on the first five days, SJT plus LT placebo on the last two days. Each group will be treated for seven days and followed-up 1–2 times. The primary outcome measures of effective rate and recurrence rate are symptoms. Secondary outcome measures of effective rate and recurrence rate are the urine leukocytes, bacteriology examination, and safety assessment. Outcomes will be assessed at baseline and after treatment.

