### Sample size

The effective rate will be taken as the main outcome measure of the clinical trial. According to a previous study, it showed that the effective rate of SJT was 77.14% in the treatment of simple bacterial lower urinary tract infection [25]. On the basis of a 0.9 power to detect a significant difference (α = 0.01, two-sided), 76 participants will be required for each group. 228 participants will be required for the three groups in a 1:1:1 ratio. Considering a 20% drop-out rate, we plan to include 252 patients in the whole trial.

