## Randomization and allocation concealment

Randomization will be used for patient allocation [31]. The randomization will be performed by an independent statistician. The random numbers are divided into three groups sequentially: experimental group; control group 1; and control group 2. SAS 9.1.3 statistical software PROC PLAN procedure statements will be used, the seed number given, and randomized grouping tables will be generated for the 252 patients receiving treatment. On-site drug blinding will be carried out, and emergency unblinding procedures will be created. Blinded materials will be kept by a full-time investigator who will not participate in any part of the trial. During the trial, the investigator will be able to obtain the randomized number and drug number of each patient from the designated central randomized platform.

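### The total of 252 patients allows for 9.5% drop-out, not the stated 20%; at 20% about 67 per group remain against the 76 required

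*Protocol article*

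**What the plan says.** The Sample size section builds the total in three steps. First, "76 participants will be required for each group", for 90% power at a two-sided α of 0.01. Second, "228 participants will be required for the three groups in a 1:1:1 ratio". Third, "Considering a 20% drop-out rate, we plan to include 252 patients in the whole trial".

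The same total appears in the abstract, in the Secondary outcome measure section under Effective rate, and in the Discussion. It is also fixed operationally under Randomization and allocation concealment: "randomized grouping tables will be generated for the 252 patients receiving treatment". No other drop-out rate and no other basis for 252 is given.

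**The concern.** The step from 228 to 252 adds 24 patients, which is too few for a 20% allowance. The purpose of the allowance is that the required 76 per group are still evaluable after losses. If the total does not contain it, the power statement fails under the protocol's own drop-out assumption.

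This matters more here than in a superiority trial analysed only by intention to treat. Both main aims under Objective and design are non-inferiority tests, and Data analysis plans an efficacy analysis in a per-protocol set limited to patients who complete without violation. The design itself creates losses from that set. Under Inclusion criteria, the urine culture runs alongside treatment, so a patient whose isolate proves not sensitive to levofloxacin is identified only after treatment has started. Exit criteria remove patients included in error, poor compliers, those given other medicines and those whose symptoms do not improve. Losses above 9.5% are therefore plausible.

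**Working it through.** **Inputs, all from the Sample size section:** required n per group 76; three groups, 1:1:1; drop-out 20%; planned total 252; power 0.90; α 0.01, two-sided.

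**Step 1, the base.** 3 × 76 = 228. The plan's figure is reproduced.

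**Step 2, the inflation for 20% drop-out.**

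| Convention | Calculation | Total | Equals 252? |
|---|---|---|---|
| n/(1 − d), correct | 228/0.80 | 285 (95 per group) | no, 33 short |
| n × (1 + d), incorrect but common | 228 × 1.20 = 273.6 | 274 | no, 22 short |
| n × (1 + d), rounded up per group | 76 × 1.20 = 91.2, so 92; 3 × 92 | 276 | no, 24 short |

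The plan's 252 is not reproduced under any of these, and rounding cannot close the gap.

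**Step 3, what 252 does allow for.**
- As a loss: 1 − 228/252 = 9.5%.
- As an add-on: 252/228 − 1 = 10.5%.

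Two origins would fit, and the text does not decide between them:
- 76 × 1.10 = 83.6, rounded up to 84 per group, gives 252. In that case the 20% is the wrong figure.
- 70 × 3 = 210, and 210 × 1.20 = 252. In that case the base of 76 is the wrong figure.

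**Step 4, what remains at 20% loss.** 252 × 0.80 = 201.6 patients, or 84 × 0.80 = 67.2 per group. Against 76 that is about 9 per group short (9/76 = 12%).

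**Step 5, power at 67 per group.** If 76 per group gives 90% power, the standardised effect at n = 76 is z(1−α/2) + z(0.90), and it scales with √n. Neither the comparator rate nor a margin is needed.

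- Two-sided α 0.01 (Sample size): (2.576 + 1.282) × √(67/76) − 2.576 = 3.858 × 0.939 − 2.576 = 1.046, so power is about 85%.
- Two-sided α 0.05 (the level in Data analysis): (1.960 + 1.282) × √(67/76) − 1.960 = 1.084, so power is about 86%.

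The same scaling applies to a non-inferiority test sized for 90% at 76: about 85% at one-sided 0.005 and about 86% at one-sided 0.025.

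**The case against.** The arithmetic itself has no defence: all the figures stand in one paragraph, and the total recurs elsewhere, so it is not an isolated misprint. The case on the other side concerns the size of the consequence.

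First, Data analysis defines the intention-to-treat set as all randomised patients. If everyone randomised is counted, that set has 84 per group, more than 76, and the shortfall does not arise there. This stands, and it limits the point to completers and the per-protocol set. It does not remove the point, because a drop-out allowance exists to protect exactly those numbers, and the per-protocol result carries weight in a non-inferiority comparison.

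Second, power falls only from 90% to about 85%, and only if the full 20% is lost. The type I error is untouched. This also stands: the trial is not invalidated.

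Third, nobody outside the trial can tell which figure is wrong. Replacing 20% by a back-calculated 9.5% would give the paragraph a drop-out expectation that has no support in the document. That is a fair caution about the remedy, and it is why the authors must identify the faulty figure.

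**Conclusion.** The point holds. As written, 76 per group, 20% drop-out and a total of 252 cannot all be true. The total is 33 patients (11 per group) below what 20% requires, and it covers 9.5%.

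Under the protocol's own drop-out rate, about 67 evaluable patients per group remain, with power of about 85% rather than 90% at two-sided α 0.01. This rests on three assumptions: that 76 per group does give 90% power, that losses fall equally on the groups, and that drop-outs leave the analysis in question. The first cannot be checked, because the section gives an effective rate of 77.14% for Sanjin tablets but neither a comparator rate nor a non-inferiority margin. That is a separate matter and does not affect the drop-out arithmetic.

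**What to change.** State which figure is wrong and make the paragraph agree with itself.

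- **If 76 and 252 are right and the 20% is not:** say that 252 patients (84 per group) allow for 9.5% drop-out.
- **If 20% is the real expectation and enrolment stays at 252:** say that about 67 per group will be evaluable and that power in completers is about 85%.
- **If the base of 76 is wrong:** correct it and redo the allowance by division. A base of 70 per group would still not be protected, since 210/0.80 = 262.5 exceeds 252.
- **If both 20% loss and 90% power in completers are to be kept:** the total is 285.

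Whichever applies, say which analysis set the required number refers to, and recompute the power for the non-inferiority hypothesis once its margin is stated.

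The first two options cost one sentence and a slightly less favourable stated allowance or power, with no change to enrolment or to the randomisation list. Only the last adds patients, 33 in all.

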### Participants and recruitment

#### Diagnostic criteria of western medicine and traditional Chinese medicine

The western medicine diagnostic criteria of acute uncomplicated lower UTI will refer to the *Guidelines for the diagnosis and treatment of urological diseases in China* (2014 ed) [26]. The traditional Chinese medicine (TCM) diagnostic criteria of acute uncomplicated lower UTI will refer to the *Clinic terminology of traditional Chinese medical diagnosis and treatment-syndromes*, *Internal Medicine of TCM* [27–29]. According to the characteristics and functions of SJT, it is proposed to select the syndrome of dampness-heat in the lower jiao as the syndrome of TCM in this trial.

#### Inclusion criteria

Inclusion criteria are as follows: (i) age > 18 and < 50 years; (ii) meet the western diagnostic criterion of acute uncomplicated lower UTI [26] that the disease duration does not exceed 72 h; (iii) bacterial culture result will be sensitive to levofloxacin (bacterial culture and clinical treatment will be conducted at the same time); (iv) the syndrome differentiation of TCM is syndrome of dampness-heat in the lower jiao; (v) did not receive antibiotic treatment within 48 h before being selected; (vi) not pregnant or lactating; and (vii) sign the written informed consent form for the clinical trial.

#### Exclusion criteria

Exclusion criteria are as follows: (i) allergic to the test drug or quinolones; (ii) there was a history of bacterial culture that was not sensitive to levofloxacin; (iii) diagnosed as complicated UTI; (iv) patients with urinary calculi or obstruction, urinary tuberculosis, renal papillary necrosis, perinephric abscess, or neurogenic bladder; (v) combined with vaginitis symptoms, genital ulcers, or gonorrhea; (vi) combined with severe cardiopulmonary disease, liver and kidney disease, advanced tumor, and other serious or progressive disease; (vii) have a neurological or mental illness and not able to cooperate; (viii) use of other antibacterial drugs in combination; (ix) pregnant, lactating, planning to become pregnant women; (x) taking part in another clinical trial within three months before being selected.

#### Exit criteria

Patients will leave the trial when one of the following criteria is met: (i) incorrectly included; (ii) are poorly compliant or pregnant; (iii) no medication or any follow-up records; (iv) occurrence of allergic reactions or serious adverse events (AE); (v) participants have other complications or special physiological changes during the trial; (vi) patients have been treated with other medicines during the trial; and (vii) not alleviated or the symptoms are aggravated. Participants may withdraw from the study at any time for any reason.

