### Blinding

This is a double-blind (patients and clinicians are blinded) and double-dummy study [30]. A two-stage blind design was used. The first stage was group A, group B, and group C; the second stage was randomization to the experimental group, control group 1, and control group 2 according to SAS software, without correspondence to group A, group B, and group C. Treatment assignments will not be revealed until the whole process is complete. If patients have severe AEs, clinicians will log on to the central platform to unblind the patients as an emergency and provide relevant treatment. Once the blinding is broken, the patient with this number will be withdrawn from the trial and the clinicians will record the reasons in the case report form (CRF). To achieve blinding, all three groups will use the same kind of packaging to encase the drug or placebo. Size, color, shape, taste, smell, and packaging of the placebo are made identical to that of the corresponding medicine by adding artificial pigment.

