## Follow-up

All included patients will be re-evaluated after seven days of treatment follow-ups as an outpatient to assess the efficacy and safety. The patients who were cured will receive the second follow-up after 28 days to assess the recurrence rate. Patients whose symptoms worsened will receive a supply of relevant medicine and a written withdrawal schedule. Assessment of study endpoints and duration of follow-up is shown in Fig. 2.

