#### Primary outcome measure

The symptoms of acute uncomplicated lower UTI will be assessed. The assessment tools for symptoms of acute uncomplicated lower UTI are three participant self-rating scales (see Additional file 2): criteria sheet for evaluating the severity of urinary system infection (CSESUSI; mild: total score ≤ 8, moderate: total score 9–15, severe: total score ≥ 16), if the severity of the disease decreases from severe to moderate, or from moderate to mild, the symptoms are improved; symptoms score sheet of TCM (SSST; cure: total score = 0, effective: total score 0–6, invalid: total score ≥ 6); overactive bladder symptom score (OABSS; if the urgent urination score > 2 and total score > 3, OAB will be diagnosed; mild: total score ≤ 5, moderate: total score 6–11, severe: total score ≥ 12). The CSESUSI will use a scoring method to record the changes of symptoms and signs before and after treatment, such as shivering, fever, dysuria, urinal pain, urinary urgency, urinary frequency, lower abdomen distending pain, lumbago, and percussion tenderness over kidney region. The SSST uses a scoring method to record the changes of symptoms, tongue, and pulse in TCM before and after treatment. The OABSS has been found to be reliable and valid and highly responsive to treatment-related fluctuations in overactive bladder symptoms. Repeating the test after an acceptable treatment interval is an effective way to assess the efficacy of a particular drug regimen on OAB symptoms [33, 34]. If the symptoms disappeared after seven days of treatment, it indicates that the patient is cured. If these symptoms partially disappeared after seven days of treatment, it indicates that the treatment is effective but not cured. If there was no obvious remission and the symptoms of infection persisted after seven days of treatment, it indicates that the treatment is invalid.

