#### Criteria of comprehensive efficacy

(i)Criteria of cure: the evaluation of clinical symptoms reached the level of cure after seven days of treatment; the value of urine leukocytes returned to the normal value; the original infected bacteria was cleared after seven days of treatment. All three criteria must be met.(ii)Criteria of effective treatment: the clinical symptoms were alleviated but did not reach the level of cure after seven days of treatment; the value of urine leukocytes was reduced but not returned to normal after seven days of treatment. Either of these criteria must be met.(iii)Criteria of invalid treatment: the clinical symptoms were not alleviated after seven days of treatment; the value of urine leukocytes was still higher than normal after seven days of treatment; the original infected bacteria were still cultured from the original infection position after seven days of treatment. All three criteria must be met.

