### Data analysis

Data analysis will be performed by professional statisticians using SPSS 22.0. Three datasets will be conducted: intention-to-treat; per-protocol set; and safety dataset. The intention-to-treat refers to the patients who have been randomized; an intentional analysis will be conducted for curative effect. The per-protocol set refers to all cases that do not violate the protocol and complete the trial; per-protocol set analysis will be conducted for curative effect. The safety dataset refers to the randomized cases that have taken a tested drug at least once with safety evaluation data after treatment. We use mean ± standard deviation (SD) for continuous variables and percentages for categorical variables. In measured indices, the independent t-test will be used for hypothesis testing of the normal variables, while the Wilcoxon rank sum test will be used for hypothesis testing of the skewed variables. The χ^2^ test will be used for hypothesis testing of the counted indices. The statistical analyses will use the two-sided hypothesis test. *P* ≤ 0.05 will be set as the significant level.

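### Failures that exit early under criteria (vi) and (vii) are excluded from the per-protocol efficacy comparison because of their outcome, and their day-7 status in the ITT set is unclear

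*Protocol article*

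**What the plan says.** All references are to the Protocol article.

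- **Exit criteria.** Exit is mandatory: "Patients will leave the trial when one of the following criteria is met". The list ends with "vi) patients have been treated with other medicines during the trial; and (vii) not alleviated or the symptoms are aggravated". Criterion (vii) carries no time point.
- **Follow-up.** "All included patients will be re-evaluated after seven days of treatment follow-ups as an outpatient to assess the efficacy and safety". The same paragraph adds: "Patients whose symptoms worsened will receive a supply of relevant medicine and a written withdrawal schedule".
- **Primary outcome measure (effective rate).** "If there was no obvious remission and the symptoms of infection persisted after seven days of treatment, it indicates that the treatment is invalid".
- **Data analysis.** "The per-protocol set refers to all cases that do not violate the protocol and complete the trial". Curative effect is analysed in this set. It is also analysed in an intention-to-treat (ITT) set of all randomised patients. Neither set is named as primary.
- **Objective and design.** Both main aims are non-inferiority tests against control group 1: control group 2 for reducing antibiotic use, and the experimental group for substituting it.

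**The concern.** A patient whose symptoms do not improve, or get worse, has what the primary measure calls an *invalid* result. The exit rule takes the same patient out of the trial, and the per-protocol definition then removes anyone who did not complete it. Membership of an efficacy set would thus depend on the efficacy outcome. Criterion (vi) works the same way for a patient rescued with another antibacterial.

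In a non-inferiority trial this matters more than usual. Removing failures raises the apparent effective rate in every arm, and raises it most where failures are most common. A truly worse test arm then looks closer to levofloxacin than it is, in a set that is commonly read as a safeguard against a false non-inferiority claim.

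**Working it through.** **1. Is the overlap real?** Exit (vii) covers symptoms that are not alleviated or are aggravated. The symptom-level *invalid* category covers symptoms that persist without obvious remission after seven days. They describe the same clinical state; only the time point differs, and (vii) has none. A patient who meets (vii) before day 7 leaves, does not complete, and is outside the per-protocol set.

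**2. Inputs.** The plan gives no figure on this point to reproduce. From the Sample size section: SJT effective rate 77.14%, and 252 patients in three equal arms, so 252/3 = 84 per arm. The section gives no levofloxacin rate, no non-inferiority margin and no share of failures that exit. Assumed here: levofloxacin rate 87.14% (a 10-point true deficit), and the same share *f* of failures exiting early in both arms.

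**3. Size of the group.** Failures expected among 84: 84 × 0.2286 = 19.2 on SJT and 84 × 0.1286 = 10.8 on levofloxacin. With *f* = 0.5, about 9.6 and 5.4 of them leave.

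**4. Rate among completers.** With true rate *p*, the completer rate is p / [p + (1 − p)(1 − f)]. For *f* = 0.5:
- SJT: 0.7714 / (0.7714 + 0.1143) = 0.871
- Levofloxacin: 0.8714 / (0.8714 + 0.0643) = 0.931

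| *f* | SJT | Levofloxacin | Apparent deficit |
|---|---|---|---|
| 0 | 77.1% | 87.1% | 10.0 points |
| 0.25 | 81.8% | 90.0% | 8.2 points |
| 0.50 | 87.1% | 93.1% | 6.0 points |
| 0.75 | 93.1% | 96.4% | 3.3 points |
| 1 | 100% | 100% | 0 |

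**5. When does the deficit shrink?** With equal *f*, the slope of the completer rate in *p* is (1 − f) / (1 − f + fp)². This is below 1 whenever p > √(1 − f) / [1 + √(1 − f)], a threshold that is always under one half. So for effective rates above 50% a true deficit shrinks at any common *f*. If the exit shares differ, the result can go either way. With *f* = 0.5 on SJT and 0.25 on levofloxacin, the deficit shows as 90.0 − 87.1 = 2.9 points. With the shares reversed it shows as 93.1 − 81.8 = 11.3 points.

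**6. Effect on the false-claim rate.** Assume a margin *m*, a test arm truly worse by exactly *m*, 84 randomised per arm, an unpooled Wald test at one-sided 0.025, and analysis of completers only. The chance of declaring non-inferiority is Φ[(d + m)/SE − 1.96], where *d* is the apparent difference. Example with *m* = 10 points, control 90%, *f* = 0.5: the completer rates are 0.9474 and 0.8889, so *d* = −0.0585. The numbers retained are 79.8 and 75.6, SE = 0.044, and the result is 15.5% against a nominal 2.5%.

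| Margin | Control rate | *f* = 0.25 | *f* = 0.50 | *f* = 0.75 |
|---|---|---|---|---|
| 10 points | 77.14% | 3.9% | 7.6% | 22.7% |
| 10 points | 90% | 5.7% | 15.5% | 53.3% |
| 15 points | 77.14% | 4.5% | 10.5% | 37.1% |
| 15 points | 90% | 7.2% | 23.9% | 76.9% |

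**7. The ITT set.** If every exit under lack of effect or rescue is counted as *invalid*, the true 10-point deficit is preserved. If exits are instead dropped for want of a day-7 result, the table in step 4 applies to the ITT set too. Which case holds depends on whether the exit rule or the Follow-up statement governs, and the article supports both.

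**The case against.** The case against a broader claim is good, and much of it stands.

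- A reader might infer that failures vanish from the efficacy comparison altogether. They do not: the ITT set contains all randomised patients and is also analysed for curative effect.
- A reader might infer that exited patients have no day-7 outcome. The article does not establish this. Follow-up has all included patients re-evaluated, the Secondary outcome measure section speaks of assessing all 252 participants, and Safety assessments has all patients tested at the end of the trial. The texts conflict; neither prevails on its face.
- A reader might equate exit (vii) with the trial's full definition of failure. The comprehensive rule opens with "Criteria of invalid treatment: the clinical symptoms were not alleviated after seven days of treatment" but also requires raised urine leukocytes and persistent bacteria, all three together. Only the symptom-level category matches.
- If (vii) is applied only at the day-7 visit, the patient already has an *invalid* result. Whether that patient then counts as having completed the trial is not clear.
- The direction is conditional, as step 5 shows. With equal failure and exit rates the levels are inflated but the difference is not.
- Exits for allergic reactions or serious adverse events, or after unblinding ("Once the blinding is broken, the patient with this number will be withdrawn from the trial"), are not efficacy failures. Nothing shown says which arm would have more, and scoring them all as *invalid* would be debatable.
- The scoring of withdrawn patients may sit in an analysis plan that is not shown, so its absence here is not a fault.

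None of this rescues the per-protocol definition. That definition and the exit rule are stated in this document, and together they exclude early failures. An analysis plan could score exits, but it could not recover day-7 urine and culture results that were never collected.

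**Conclusion.** The point holds for the per-protocol efficacy set: followed as written, the plan excludes early-exiting failures and rescued patients on the basis of outcome. If the test arm fails more often and the exit shares are similar, its deficit shrinks toward non-inferiority: 10 points shows as 8.2, 6.0 or 3.3 when 25%, 50% or 75% of failures exit. The levofloxacin rate, exit shares and margins are assumptions, so these figures show the mechanism and its range and do not forecast the result. The case where all failures exit is a limit only.

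For the ITT set the conclusion is narrower. The patients are retained, but the Exit criteria and Follow-up sections contradict each other on whether they are assessed at day 7. The documents do not support saying that the ITT comparison is biased, or that the bias must favour non-inferiority.

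**What to change.** Reconcile Exit criteria, Follow-up, Primary outcome measure and Data analysis, leaving the clinical decisions on stopping and rescue as they are:

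1. State that leaving study treatment under (vi) or (vii) does not end outcome collection, and that the day-7 assessment already planned in Follow-up is kept for every randomised patient.
2. In the ITT analysis, count exit for lack of effect, or for treatment with another antibacterial, as *invalid*. Criterion (vi) covers any other medicine; exits for an unrelated medicine need not be scored this way.
3. Amend the per-protocol definition so that exit for lack of effect or rescue counts as an *invalid* outcome and is not a reason for exclusion.

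The 28-day visit is planned only for cured patients and need not change. The cost is wording, plus day-7 assessment of exited patients at a visit already in the schedule. Effective rates will be slightly lower in all arms.

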## Method/design

### Objective and design

This is a randomized, double-blind, double-dummy, parallel control of positive drug, multicentre clinical study. The study will be conducted at: the XiYuan Hospital, China Academy of Chinese Medical Sciences; the Longhua Hospital Shanghai University of Traditional Chinese Medicine; the Guangdong Provincial Hospital of Traditional Chinese Medicine; the Hubei Hospital of Traditional Chinese Medicine; the Affiliated hospital of Chengdu University of Traditional Chinese Medicine; and the Yunnan Provincial Hospital of Traditional Chinese Medicine. Ethical clearance for the trial was obtained from ethics committee of the six hospitals. Patients with acute uncomplicated lower UTI will undergo a standardized baseline evaluation before treatment, comprising detailed history taking, physical examination, and laboratory testing. All included patients are randomly divided into three groups: experimental group; control group 1; and control group 2. The experimental group receives SJT plus levofloxacin tablets (LT) placebo; control group 1 receives LT plus SJT placebo; and control group 2 receives SJT plus LT on the first five days, SJT plus LT placebo on the last two days. After seven days of treatment, the efficacy and safety of three groups will be evaluated. The first aim is to determine whether SJT can reduce the use of antibiotics (control group 2 versus control group 1, non-inferiority test); the second aim is to determine whether SJT can substitute the use of antibiotics (experimental group versus control group 1, non-inferiority test). The recurrence rate will be assessed at the 28-day follow-up after being cured to determine whether SJT can reduce the recurrence rate. The trial is conducted in accordance with the World Medical Association Declaration of Helsinki and Good Clinical Practice of Pharmaceutical Products [17, 18]. After a full explanation by the clinicians, written informed consent will be obtained from the participants before intervention [19, 20]. Strict data management and quality control will be conducted in this trial [21, 22]. This trial was registered in the Clinical Trials USA registry (registration No. NCT03658291) on 4 September 2018 and will be carried out from January 2019 to December 2019. The study design is shown in Fig. 1. The protocol follows the recommendations of the SPIRIT initiative (see Additional file 1) [23] and the trial results will be reported according to the latest version of the CONSORT statement [24].

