#### Primary outcome measure

(i)The recurrence rate of cured participants will be assessed by the symptoms of acute uncomplicated lower UTI. The assessment tools of renewed symptoms will also use the three participant self-rating scales (see Additional file 2): CSESUSI; SSST; and OABSS. If the symptoms of cured patients reappeared in the fourth week after the end of medication, it indicates the participant has relapsed.

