### Safety assessments

Safety measurements included laboratory indices and AEs. All patients will undergo the following laboratory examination before enrollment and at the end of the clinical trial. Changes in laboratory indices before and after the clinical trial will be compared to conducting a safety analysis. Laboratory indices are: (i) routine blood and urine testing; (ii) liver function (AST, ALT, TBIL, DBIL, γ-GT, ALP) and kidney function (Scr, BUN); and (iii) ECG. The occurrence of any AEs in trial participants, such as subjective discomfort of patients and abnormal laboratory results, will be recorded in the CRF during the whole trial process. We will withdraw patients who have severe AEs, as it will be unsafe for them to continue the trial. Meanwhile, we will give them relevant medical care and follow them up until the reaction has terminated.

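### Exit criterion (vi) removes any patient treated with another medicine, without limit by drug class or period, so cured patients can lose their primary recurrence outcome, including those treated for an early recurrence

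*Protocol article*

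**What the plan says.** The Exit criteria section opens with a mandatory rule: "Patients will leave the trial when one of the following criteria is met". Item (vi) of the list is that "patients have been treated with other medicines during the trial". It gives no drug class, no indication and no period other than the trial itself.

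The trial does not end with the seven days of treatment. Objective and design states: "The recurrence rate will be assessed at the 28-day follow-up after being cured to determine whether SJT can reduce the recurrence rate". Follow-up states: "The patients who were cured will receive the second follow-up after 28 days to assess the recurrence rate". Under Recurrence rate, the primary outcome measure reads: "The recurrence rate of cured participants will be assessed by the symptoms of acute uncomplicated lower UTI". A patient counts as relapsed under this condition: "If the symptoms of cured patients reappeared in the fourth week after the end of medication".

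The only follow-up after withdrawal that the article describes is in Safety assessments. It concerns patients withdrawn for severe adverse events, whom the investigators will "follow them up until the reaction has terminated". Data analysis defines intention-to-treat as the randomized patients, and the other efficacy set as follows: "The per-protocol set refers to all cases that do not violate the protocol and complete the trial".

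**The concern.** The consequence of item (vi) is leaving the trial, not merely stopping study drug. Recurrence by symptoms is labelled primary and is measured only in cured patients, so each exit shrinks a group that is already smaller than the arm.

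Two kinds of patient can be lost:

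- **A cured patient who takes something unrelated**, for example a cold remedy in the third week. The outcome is lost for a reason that may have nothing to do with the infection. The cost is precision.
- **A cured patient whose symptoms return early** and who is given an antibacterial before the 28-day visit. This patient has the very event being counted and leaves before it is assessed. The cost is a recurrence rate that is too low.

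The second case arises even if the rule is read narrowly, and it is the more serious of the two.

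**Working it through.** **Step 1. What the text fixes.** Exclusion criterion (viii) is limited to antibacterials, and inclusion criterion (v) to antibiotics. Exit criterion (vi) carries no such limit. The Abstract describes each group's course as seven days of treatment plus one or two follow-ups, so the 28-day visit falls within the trial. No section restricts item (vi) to the treatment week or provides for efficacy visits after exit. Intention-to-treat membership keeps the patient in the set but does not supply a 28-day outcome that nobody observed.

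**Step 2. Literal reading: outcomes lost.** The plan has no figure of its own to reproduce here. It gives neither the use of other medicines nor a cure rate.

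Inputs:
- Patients per arm: 252 / 3 = 84 (Sample size).
- Weekly chance w of taking an unrelated medicine: 1%, 3% or 5% (assumed).
- Cured share c: 30%, 50% or 70% (assumed).
- Time at risk: four weeks after day 7.
- Enforcement: everyone who takes one leaves (assumed).

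Share of cured patients lost: p = 1 − (1 − w)^4. Outcomes lost per arm: 84 × c × p. Factor by which the confidence interval for a between-arm difference widens: 1/√(1 − p), whatever c and the recurrence rate.

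| w | p | lost, c = 30% | lost, c = 50% | lost, c = 70% | CI width factor |
|---|---|---|---|---|---|
| 1% | 1 − 0.99^4 = 3.9% | 1.0 | 1.7 | 2.3 | 1.020 |
| 3% | 1 − 0.97^4 = 11.5% | 2.9 | 4.8 | 6.7 | 1.063 |
| 5% | 1 − 0.95^4 = 18.5% | 4.7 | 7.8 | 10.9 | 1.108 |

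With 42 cured per arm (84 × 50%) and an assumed 20% recurrence in both arms, the 95% half-width is 1.96 × √(2 × 0.2 × 0.8 / 42) = 17.1 percentage points. Replacing 42 by 42 × (1 − p) gives 17.5, 18.2 or 19.0 points.

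**Step 3. Narrow reading: antibacterials only.** Let r be the true share of cured patients who recur before or at the visit, and t the share of those recurrences treated with an antibacterial before it. Neither is in the documents, so the result is left in symbols.

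- If treated patients exit and drop out of the denominator, the observed rate is r(1 − t)/(1 − rt). This is below r whenever t is above 0 and r is below 1.
- If they stay to the visit but are judged only on symptoms in the fourth week, and treatment has cleared them, the observed rate is r(1 − t). This is lower still.

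Keeping the visit is therefore not enough by itself. A counting rule is needed as well.

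**The case against.** The strongest reply is that the broad reading is not the intended one. The neighbouring eligibility criteria speak of antibacterials. No eligibility criterion bars a patient already on an unrelated medicine, yet the literal rule would eject that patient at enrolment. Follow-up promises the second visit to cured patients without exception. The article also condenses a protocol that is not shown and may list the prohibited medicines and their window.

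Much of this stands as inference. The cold-remedy case is an illustration, and the literal reading is one of several. But the article prints a mandatory rule with a stated consequence, and nothing printed narrows it. This is a rule worded too widely, not a detail left out. The narrow reading also leaves the early treated recurrence unprotected.

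A second reply is that the precision loss is small and rests wholly on assumed inputs. It adds that the trial is sized on the effective rate, with no stated power target for recurrence, and that a half-width of about 17 points is imprecise anyway. That is correct, and it is why the point stays minor.

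A reader might go further and infer two stronger claims:

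- **That the rule biases the comparison between arms.** Unrelated medicines should fall similarly across blinded arms. For treated recurrences, the documents give no rates by arm from which a direction could be derived.
- **That it shifts the day-7 per-protocol results.** The requirement to complete the trial could be read as removing a patient who exits after day 7. But Data analysis ties that set to curative effect, which is judged at day 7, so the text does not settle the matter. Recorded day-7 results stay in the intention-to-treat set in any case.

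**Conclusion.** The point holds as a minor one. As printed, exit criterion (vi) sends out any patient treated with another medicine at any time in the trial, and no printed text retains such patients for efficacy.

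On the literal reading applied to the 28-day visit, the effect is a modest loss of precision in the primary recurrence outcome. Under the assumptions shown, the confidence interval is 2.0% to 10.8% wider. These figures rest on assumed medicine use, cure rate and full enforcement; the half-widths also rest on an assumed recurrence rate. The true size cannot be obtained from the documents.

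On the antibacterials-only reading, the unrelated-medicine loss disappears. The outcome-related loss remains: cured patients treated for an early recurrence are removed before they can be counted, which understates recurrence by an amount the documents do not allow one to compute.

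**What to change.** 1. Limit exit criterion (vi) to antibacterials and other medicines able to affect urinary symptoms, urine leukocytes or culture, in a short list agreed before unblinding.
2. Make use of a listed medicine a recorded protocol deviation, with study drug stopped if needed, and not an exit from follow-up. Keep the day-7 and 28-day visits for everyone due them.
3. Count a cured patient given an antibacterial for returned urinary symptoms before the 28-day visit as a recurrence, whatever the symptoms at the visit.
4. Record all other medicines as concomitant medication. Define per-protocol status at each assessment only by listed medicines taken before it.

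The cost is one reworded criterion, one short list and one counting rule, with no visits beyond those already planned. The small downside is that a few patients whose unrelated medicine slightly alters symptoms stay in the per-protocol set.
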